## Abstract

**Background:**

Sexual and gender minority youth (SGMY, aged 14-29 years) face increased risks to their well-being, including rejection by family, exclusion from society, depression, substance use, elevated suicidality, and harassment, when compared with their cisgender, heterosexual peers. These perils and a lack of targeted programs for SGMY exacerbate their risk for HIV and other sexually transmitted infections. Cognitive behavioral therapy (CBT) interventions support clients by generating alternative ways of interpreting their problems and beliefs about themselves. CBT, tailored to the experiences of SGMY, may help SGMY improve their mood and coping skills by teaching them how to identify, challenge, and change maladaptive thoughts, beliefs, and behaviors. Based on the promising results of a pilot study, a CBT-informed group intervention, AFFIRM, is being tested in a pragmatic trial to assess its implementation potential.

**Objective:**

The aim of this study is to scale-up implementation and delivery of AFFIRM, an 8-session manualized group coping skills intervention focused on reducing sexual risk behaviors and psychosocial distress among SGMY. Our secondary aim is to decrease sexual risk taking, poor mental health, and internalized homophobia and to increase levels of sexual self-efficacy and proactive coping among SGMY.

**Methods:**

SGMY are recruited via flyers at community agencies and organizations, as well as through Web-based advertising. Potential participants are assessed for suitability for the group intervention via Web-based screening and are allocated in a 2:1 fashion to the AFFIRM intervention or a wait-listed control in a stepped wedge wait-list crossover design. The intervention groups are hosted by collaborating community agency sites (CCASs; eg, community health centers and family health teams) across Ontario, Canada. Participants are assessed at prewait (if applicable), preintervention, postintervention, 6-month follow-up, and 12-month follow-up for sexual health self-efficacy and capacity, mental health indicators, internalized homophobia, stress appraisal, proactive and active coping, and hope. Web-based data collection occurs either independently or at CCASs using tablets. Participants in crisis are assessed using an established distress protocol.

**Results:**

Data collection is ongoing; the target sample is 300 participants. It is anticipated that data analyses will use effect size estimates, paired sample *t* tests, and repeated measures linear mixed modeling in SPSS to test for differences pre- and postintervention. Descriptive analyses will summarize data and profile all variables, including internal consistency estimates. Distributional assumptions and univariate and multivariate normality of variables will be assessed.

**Conclusions:**

AFFIRM is a potentially scalable intervention. Many existing community programs provide safe spaces for SGMY but do not provide skills-based training to deal with the increasingly complex lives of youth. This pragmatic trial could make a significant contribution to the field of intervention research by simultaneously moving AFFIRM into practice and evaluating its impact.

**International Registered Report Identifier (IRRID):**

DERR1-10.2196/13462

## Introduction

### Intersecting Vulnerabilities of Sexual and Gender Minority Youth

Compared with their cisgender, heterosexual peers [1-8], sexual and gender minority youth (SGMY, aged 14-29 years) face increased risks to their well-being, including rejection by family [9], exclusion from society [10], depression [10,11], substance use [12], elevated suicidality [13,14], and harassment [15-19]. In the pilot study that informed this protocol, participants attributed the stress of their SGM status as a significant contributor to their risks [20]. Yet, there remains a dearth of research and services for SGMY [21]. Existent risks and the lack of targeted programs [21-25] exacerbate their risk for HIV infection [12,26]. In 2013, nearly 25% of the 2090 Canadians diagnosed with HIV were aged between 15 and 29 years, and 43% of those youth contracted HIV through same-sex exposure (compared with only 26% in 2004) [12,26,27].

There is a particular lack of research with female-identified SGMY, who report higher rates of HIV-related risk behaviors than their male-SGMY and non-SGMY peers [28-37]. These risks include sex with multiple partners [28,29], unprotected vaginal intercourse [30], injection drug use [31], and pregnancy [32,33]. SGMY risk factors are further increased in female-identified SGMY, as they have higher rates of mental health concerns compared with male-identified SGMY, including depressive symptoms and suicidality at younger ages, suggesting earlier onset of co-occurring concerns [34-36].

Thus, multiple factors such as depression [10], sexual health-risk behaviors [31], discrimination [16] and perceptions that HIV is not a threat [28-30] may interact to exacerbate SGMYs’ risk [3]. Female-identified SGMY—as well as transgender, gender diverse, and racialized SGMY—experience even greater vulnerabilities to mental health stressors, which in turn can exacerbate sexual health risk [38-40]. Holistic interventions that affirm SGMY identities and cultivate a sense of community, may mitigate these risks [41,42]. As nearly 70% of premature adult deaths are related to behaviors initiated in adolescence (eg, unsafe sex and substance abuse) [43], this age range is a critical period to implement interventions that help youth cope with the risks they experience.

### Theoretical Approach

Syndemics, minority stress, and community-based research theories provide insight toward SGMY intervention development. Syndemics theory highlights social inequities as root causes of synergistic interaction of 2 or more coexistent issues (eg, SGMY status and depression) or mutually reinforcing epidemics (eg, HIV) contributing to health disparities among marginalized populations [40,44-47]. Vulnerable individuals may encounter lifelong adversity, particularly from social marginalization and stigma [45], posing a greater risk for problems [44,46] that can lead to poorer sexual and health outcomes [47]. For SGMY, as the number of psychosocial health problems increases, the risk of major negative health outcomes also increases [47-49]. To comprehensively combat sexual health risks, overlapping vulnerabilities must be addressed concurrently [48,49].

Minority stress theory posits that marginalized populations experience a unique form of stress because of conflict between their identities and social expectations [50-53]. It partially explains why SGMY encounter disproportionate chronic stress, discrimination, and victimization [52], which subsequently increases likelihood of sexual risk taking, depressive anxiety, and substance abuse disorders [52,53]. An influential stressor, internalized homophobia (negative beliefs about one’s own SGMY status) [54], is related to unprotected sex [54,55] and increased depression [10]. Minority stress may increase internalized homophobia and stress-related cortisol production associated with heightened depression, anxiety, and suicidal ideation [50,54]. SGMY may not learn to cope with stressors through traditional means (eg, family or community support) [55-58], resulting in vulnerability to health and mental health threats [48] and increasing likelihood of engaging in risky behaviors [49]. As traditional approaches do not address many of the co-occurring stressors for SGMY, interventions that enhance coping skills are critical [59-82].

Building on a rich history of community engagement in HIV/AIDS service delivery, community-based research is critical to intervention development with SGMY, particularly in diverse communities [83-88]. Community-based approaches build on shared values, belief systems, and social practices, allowing for discussions of HIV and sexual health-risk behaviors in a culturally sensitive manner [84-87]. Youth interventions developed in partnership with community also have a much higher rate of agency adoption than those with only academic stakeholders [88]. It is increasingly recognized that future youth interventions must include nimble design and flexible delivery [89-91]. Community feasibility studies improve an intervention’s implementation potential while maintaining rigor in evaluation [92,93].

### Affirmative Cognitive Behavioral Therapy

Cognitive behavioral therapy (CBT) suggests that people’s behaviors and emotions are influenced by their perceptions of life events [60-62] and how one interprets their situation will impact the way they feel or behave [63]. As an example, a person who is depressed may experience unhelpful interpretations or perceptions of themselves because of their problems and life events [61,62]. CBT interventions support clients by generating alternative ways of interpreting their problems and beliefs about themselves [59,63]. Generating alternative ways of thinking and beliefs may facilitate positive changes in one’s behaviors and emotional states [64].

CBT tailored to the experiences of SGMY may help improve mood and increase coping by teaching youth how to identify, challenge and change maladaptive thoughts, beliefs, and behaviors [59,66,67]. Continuing to practice CBT skills after each session (ie, via an action plan) further strengthens adaptive and affirming beliefs and behaviors. This process may lead to changing deeply ingrained problematic ways of thinking and behaving [65-67]. The process of identifying and challenging unhelpful beliefs about sexual and gender identities in an affirming and supportive environment may facilitate a decrease in internalized homo-, bi-, and transphobic cognitions and emotions and lead to improvement in mood and coping [67-69]. Ultimately, CBT within an affirmative therapeutic context can support SGMY in challenging maladaptive coping skills (eg, negative beliefs, isolation, substance misuse, and self-harm) and learning adaptive coping skills (eg, balanced thinking, enhancing social supports, and goal-setting) through education, modeling, practicing skills, and positive reinforcement [15,69]. 

CBT has been effective at treating depression and sexual health-risk behaviors among minority status adolescents [70-72] and lesbian, gay, bisexual, transgender, and queer (LGBTQ) adults [66,72]. However, its effectiveness for SGMY is largely unknown [69]. While the majority of studies do not assess long-term treatment gains, some evidence suggests that such interventions have mental and sexual health benefits for minority populations [79]. Longitudinal research is needed to determine the sustained effectiveness of CBT interventions on adolescent and young adult SGM populations [80]. A few existing studies show promise with sustained reductions in depression found at 12 months [76,77] and 18 months [78], as well as sexual risk of young men who have sex with men at 6 months [72]. Despite the calls for resilience and coping-based research and interventions for SGMY [80], scholarship has maintained a focus on negative health and psychosocial outcomes [81]. To date, no studies have identified the utility of a large-scale implementation of CBT tailored for community-based, diverse groups of SGMY and drawing on an affirmative approach. This study is designed to fill that gap.

## Methods

### AFFIRM Structure

This pragmatic trial is designed to evaluate AFFIRM, a manualized group intervention for SGMY, which follows the structure described in Textbox 1 and is described in more detail elsewhere [20].

Description of AFFIRM intervention (session focus and session activities).Session 1 focusIntroduction to cognitive behavioral therapy (CBT), exploring lesbian, gay, bisexual, transgender, and queer (LGBTQ)+ identities, and understanding minority stress.Session 1 activitiesIntroductionsDiscussing the theory and purpose of CBT approachesExploring stress and minority stressUnderstanding the causes of stress in our livesSession 2 focusUnderstanding the impact of anti-LGBTQ attitudes and behaviors on stress.Session 2 activitiesCheck in and reviewExamining homophobia, heterosexism, and transphobia at the individual, institutional, and cultural levelIdentifying how these experiences impact thoughts, feelings, and behaviorsFostering strategies for both coping with and combating anti-LGBTQ discrimination at all levelsSession 3 focusUnderstanding how thoughts impact feelings.Session 3 activitiesCheck in and reviewDistinguishing between thoughts and feelingsExploring how thoughts influence feelings and behaviorsIdentifying counterproductive thinking patternsRecognizing negative self-talk and feelings of hopelessnessLearning thought stoppingSession 4 focusUsing thoughts to change feelings.Session 4 activitiesCheck in and reviewIncreasing positive thinking and feelings of hopeChanging negative thoughts to positive thoughtsChallenging negative thinking and internalized homophobia/negative feelings through the ABCD (activating event, belief, consequence, and debate) methodSession 5 focusExploring how activities impact feelings.Session 5 activitiesCheck in and reviewExamining the impact of various activities on feelingsIdentifying supportive and identity-affirming activitiesThe impact of LGBTQ-affirming activities on feelingsSession 6 focusPlanning to overcome counterproductive thoughts and negative feelings.Session 6 activitiesCheck in and reviewDistinguishing between clear and unclear goalsIdentifying short, mid-, and long-term goalsCreating a sexual health planFostering hope for the futureSession 7 focusUnderstanding the impact of minority stress and anti-LGBTQ attitudes or behaviors on social relationships.Session 7 activitiesCheck in and reviewAnti-LGBTQ discrimination can lead to feelings of discomfort around othersResponding to discrimination or harassment in social situationsLearning to be assertiveSession 8 focusPutting it all together: developing safe, supportive, and identity-affirming social networks.Session 8 activitiesCheck in and reviewMaintaining a healthy social network: attending to thoughts, expectations, feelings, and behaviors within relationshipsIdentifying a plan for building a supportive network

### Research Questions, Hypotheses, and Objectives

This project is intended to scale-up implementation and delivery of AFFIRM, an 8-session manualized group coping skills intervention focused on reducing sexual risk behaviors and psychosocial distress among SGMY. This project aims to decrease sexual risk taking, depression, and internalized homophobia and increase levels of sexual self-efficacy and proactive coping among SGMY (ages 14-29 years). This project has the following research questions:

To what extent can AFFIRM be feasibly implemented in a range of practice settings, such as community health centers, family health teams, and community-based organizations?What are the facilitative conditions and implementation barriers to effective delivery of AFFIRM?How does participation in an affirmative coping skills intervention (AFFIRM) impact the psychosocial distress and sexual self-efficacy of SGMY?

Given these research questions, the study has the following hypotheses:

Hypothesis 1: AFFIRM can be feasibly implemented in a range of practice settings, and SGMY will have high rates of acceptability of the intervention.

Hypothesis 2: SGMY participating in AFFIRM will show significantly greater decreases in psychosocial distress (eg, internalized stigma and depression) compared with wait-listed controls (ie, SGMY attending existing community programs).

Hypothesis 3: SGMY participating in AFFIRM will show significantly higher levels of sexual self-efficacy and coping compared with wait-listed controls.

### Eligibility Criteria

#### Inclusion and Exclusion Criteria

Inclusion criteria are as follows:

Aged 14 to 29 years at the time of screeningIdentifies as a sexual and/or gender minorityReads, writes, and speaks fluent EnglishIs interested in participating in the 8-session AFFIRM Intervention.

Exclusion criteria are as follows:

Assessed by the Facilitation Team to be in crisis (ie, high risk of suicidality)Warranting a more intensive intervention

#### Trial Design

This pragmatic quasi-experimental study uses a stepped wedge wait-list crossover design (SWWCD), whereby all participants receive the intervention in clusters [94-98]. SWWCD has been utilized in community-based research where traditional randomization with a no-treatment condition is unethical, unacceptable to community stakeholders, or not feasible [98]. This study will examine the effects of participating in an AFFIRM intervention group (each consisting of 6-10 participants) compared with wait-list for SGMY (ages 14-29 years).

##### Randomization

Randomization is not possible in this study because of participants’ registration through various CCAS.

##### Blinding

Participants are not blinded as they know whether they are assigned to intervention or wait-listed control. Facilitators are blinded to outcome assessments as outcomes are administered via survey weblink.

##### Allocation

Participants are allocated in an approximate 2:1 fashion to intervention: wait-listed control. This ratio is based on the availability of practice sites to implement AFFIRM in their clinical practices [96,97]. Importantly, similar to community programming, the groups are constructed to be developmentally appropriate. Participants in a particular intervention group are typically within an age range of 3 to 5 years. For example, a 14 year old would generally not be placed in a group with anyone older than 18 years. Groups of people aged between 18 and 29 years may have a broader age range, as developmental stage is not as relevant for established adults. AFFIRM also consists of mixed identity groups (eg, sexual identities and gender identities), based on community feedback. This means that a single intervention group could comprise SGMY from a range of identities. Many community organizations do not focus on 1 particular SGM subpopulation but instead serve all SGMY.

##### Framework

This pragmatic trial is designed to assess AFFIRM’s implementation potential in real-world practice conditions.

#### Study Setting

Collaborating community agency sites (CCASs) in a variety of urban, suburban, and rural communities across Ontario, Canada, are hosting a series of AFFIRM intervention groups, each consisting of 6 to 10 SGMY (aged 14-29 years). At present, there are 23 CCAS, of which 12 are urban, 8 are suburban, and 3 are rural, with more communities likely to be added in subsequent years of the study.

#### Justification

Age group of 14 to 29 years have been identified as a crucial time for SGMY as they start to come out, address family issues, and transition to postsecondary education and early employment [1-3]; as such, this age may be the ideal time for an affirmative CBT intervention. As SGMY face greater well-being risks than their cisgender, heterosexual peers, queerness is also an important qualifier for this study [4-8]. This study focuses on English-speaking CCASs in Ontario. Commitment to an 8-session intervention and exclusion because of crisis are criteria common to group intervention research [99]**.**

### Interventions

#### AFFIRM Intervention (Experimental)

AFFIRM aims to help SGMY develop coping skills through a combination of education (delivered by facilitators) and rehearsal (ie, simulation of real-life experiences) in a manner that affirms (ie, validates) participants’ sexual and gender minority identities, as well as their experiences. Affirmations are explicated through (1) acknowledging and validating the unique struggles experienced by SGMY (eg, homophobia); (2) exploring how participants currently cope with SGM-specific stressors (eg, familial disapproval); (3) facilitating the development of realistic alternative ways of thinking and behaving that affirm youth identities and sexual health choices while integrating healthy ways of coping with internal/external stressors; and (4) enhancing social connection between participants. AFFIRM also includes an overview of sexually transmitted infections (STIs), HIV/AIDS and hepatitis C, and focuses on activities that promote harm reduction, such as a personalized sexual safety plan regardless of accumulated sexual experience. Each series of AFFIRM begins with an orientation session for introductions and discussion of the 8-session schedule. Each of the 8 group sessions of AFFIRM then consist of (1) warm-up/review; (2) discussion of session objectives; (3) behavioral activities; (4) practice and rehearsal; and (5) group reflection and summary.

#### Wait-List (Control)

If they choose, wait-listed participants will attend existing community programs, considered to be treatment as usual for community intervention studies. In a SWWCD study, sites offer iterations of the intervention in phases; individuals in this study will move from the wait-list to AFFIRM over time [94]. The wait-list time frame is minimized as much as possible to ensure an ethical research process. As it is increasingly acknowledged that evidence-based practice requires community and practice-based research [95], alternative intervention designs that are rigorous and work in *the real world* are needed. Such designs adapt to local needs and often have better intervention outcomes [96-100].

#### Discontinuation Criteria

Participants who are in crisis (eg, actively suicidal) at any point during their in-person participation in the AFFIRM intervention are immediately assessed, and appropriate steps are taken to address their individual situation—up to and including being taken to local support services or hospitals by AFFIRM facilitators. Participants who are in crisis are withdrawn from the intervention and the study. A distress protocol (Multimedia Appendix 1) and crisis response form (Multimedia Appendix 2) have been developed for AFFIRM facilitators and is systematically implemented throughout the intervention when participants indicate signs of distress. Importantly, to enhance participants’ safety and well-being, as part of the Web-based data collection, participants are asked at various points if they need immediate help and are provided with immediate resources, including national crises organizations (such as Kids Help Phone Canada or the Trevor Project) with 24-hour counseling via phone, chat, and/or SMS text messaging (short message service, SMS).

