### Harms

As a psychosocial study, risks for adverse effects are negligible or nonexistent. The study’s distress plan, discussed above, will be used if participants present in crisis.

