## Results

It is anticipated that data analyses will use effect size estimates, paired sample *t* tests, and repeated measures linear mixed modeling (LMM) using SPSS to test for differences pre- and postintervention [112-114]. Descriptive analyses will summarize data and profile all variables, including internal consistency estimates. Distributional assumptions, univariate, and multivariate normality of all variables will be assessed. Data determined to be missing at random will be imputed with the expectation-maximization method with importance re-sampling [113].

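### Withdrawing participants in crisis from the study, and not only from AFFIRM, loses outcomes that depend on distress, probably in the AFFIRM condition only

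*Protocol article*

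**What the plan says.** Under Discontinuation Criteria, people in crisis, with active suicidality as the example, who are identified "at any point during their in-person participation in the AFFIRM intervention are immediately assessed". The section then adds: "Participants who are in crisis are withdrawn from the intervention and the study". The distress protocol is a tool for AFFIRM facilitators and "is systematically implemented throughout the intervention when participants indicate signs of distress". For the web surveys the arrangement is different: "participants are asked at various points if they need immediate help and are provided with immediate resources". No withdrawal is attached to that route.

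For the control period, Wait-List (Control) says: "If they choose, wait-listed participants will attend existing community programs, considered to be treatment as usual for community intervention studies". It describes no facilitator contact or crisis assessment while waiting. Under Participant Timeline, the control outcome is the wait-list group's pretest, completed online before the first session. The AFFIRM outcome is the posttest, completed at the site after the last session.

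On missing data, the Results section says: "Data determined to be missing at random will be imputed with the expectation-maximization method with importance re-sampling".

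**The concern.** Crisis is an extreme state of the distress that Hypothesis 2 compares between conditions. A rule that ends data collection at that point removes outcomes because of their likely value. If it acts in one condition and not in the other, the AFFIRM posttest mean looks better than it is while the control mean is untouched, and the comparison tilts towards AFFIRM even when there is no effect.

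Two features make this more than a matter for the analysis stage. Outcomes that were never collected cannot be recovered by any analysis plan. And imputation from the pretest assumes that, given the pretest, those withdrawn would have scored like those who stayed. That is doubtful for a crisis that arises after the pretest and that no survey captures.

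**Working it through.** **Reading the passages side by side**

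1. *What is lost.* The posttest, the 6- and 12-month surveys and the satisfaction survey all come after the point of withdrawal. The pretest has already been collected.
2. *Where it is lost.* Assessment and the distress protocol are described for in-person AFFIRM participation. The only study contact described between allocation to the wait-list and the pretest is by web survey, where help resources are offered. The control outcome is taken before any in-person session, so the rule as described has no means of acting on it. After crossover, wait-listed participants come under the same rule, and their own pre-post change is affected too.
3. *Entry screening.* The exclusion for crisis applies to everyone before allocation, so it does not create the asymmetry.

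**Size**

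The article's only figure is a target of about 300, with no power calculation to reproduce; the point does not depend on it. Allocation of about 2:1 is taken as 200:100. The article gives no crisis rate, SD or correlation, so the following are assumptions: no true effect, distress scores standardised to SD 1, a pre-post correlation of 0.6, a fraction c withdrawn from the AFFIRM condition only, and a crisis tendency correlated 0.5 to 1.0 with the posttest.

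In the extreme case (correlation 1.0) the mean posttest of those retained shifts by −φ(z)/(1 − c), where z is the standard normal quantile at 1 − c:

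- c = 2%: −0.049 SD
- c = 5%: −0.109 SD
- c = 10%: −0.195 SD

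Missing posttests were then imputed by regression on the pretest, which is the missing-at-random logic, in simulations of 2,000,000 per cell. The change score has SD √(2(1 − 0.6)) = 0.894, so the standard error of the difference is 0.894 × √(1/100 + 1/200) = 0.109. The last column takes a nominal two-sided 5% test and ignores clustering.

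| Withdrawn | Bias left after imputation, favouring AFFIRM | Approximate type I error |
|---|---|---|
| 2% | 0.016 to 0.032 SD | 0.052 to 0.060 |
| 5% | 0.035 to 0.075 SD | 0.062 to 0.105 |
| 10% | 0.064 to 0.139 SD | 0.090 to 0.246 |

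Two boundary cases limit the claim. If crisis depended on the observed pretest alone, imputation would leave a bias of about 0.00 SD at all three rates. If outcomes were collected from everyone, or lost equally in both conditions, this bias would be zero under the null.

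In people, 2 to 5% of 200 is 4 to 10 missing posttests in the intervention-only group.

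**The case against.** The strongest reply is that this touches only exploratory scales. The primary outcomes are feasibility and acceptability, the secondary outcome is fidelity, and the sample size was set chiefly for implementation. Entry screening also removes people already in crisis, which should keep the rate low. This stands and lowers the severity. It does not remove the point: Hypotheses 2 and 3 rest on these scales, and Results expects a significant between-condition difference. The satisfaction survey also appears to feed acceptability.

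Several stronger readings are tempting, and the documents do not support them:

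- *That wait-listed youth in crisis are known to stay in the data.* No passage says so. The withdrawal sentence is unqualified; the in-person wording belongs to the sentence on immediate assessment. The asymmetry is an inference, though a natural one, from the absence of any described wait-period procedure.
- *That imputation can never repair the loss.* It could if the pretest explained crisis. Nor does the article claim that crisis withdrawals are missing at random: it imputes only data judged to be so, and what happens to the rest may be left to an analysis plan. What stands is that observed data cannot settle that judgement. The planned mixed model gives no escape, because it too assumes missing at random.
- *That deterioration vanishes from the record.* Crisis response forms and facilitator process notes exist, and completion is counted as a feasibility measure. A crisis withdrawal would at least appear as a non-completer, although no tabulation by cause is described.
- *That the Harms sentence, "As a psychosocial study, risks for adverse effects are negligible or nonexistent", adds to the bias.* It concerns harms reporting, which is a separate matter, and the same section refers to the distress plan.

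Finally, surveys take about 20 minutes, and participants may be as young as 14. Contacting someone just withdrawn in crisis is an ethics decision as well as a change of wording. This is accepted, and the change below is conditional on it.

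**Conclusion.** The concern holds in limited form and should be fixed. Following the rule as written leaves later outcomes uncollected for a reason tied to the distress outcome, probably in the AFFIRM condition only, and the direction favours AFFIRM. If 2 to 5% reach crisis, about 0.02 to 0.08 SD of spurious benefit would remain after imputation, with type I error of roughly 0.05 to 0.11. At the lower rate the effect is small.

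These sizes rest on an assumed crisis rate, assumed correlations and a crisis tendency not fully explained by the pretest. The direction also rests on the inferred absence of equivalent withdrawal during the wait. A reader might infer that all data from these participants are deleted; the article says nothing of the kind about the pretest. No view is taken on when AFFIRM should be stopped.

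**What to change.** Leave the clinical handling of crisis and the decision to stop AFFIRM unchanged. Then:

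1. Amend the part of the sentence that withdraws these participants from the study. Those who agree, and for whom contact is judged appropriate under the distress protocol and by the ethics board, are still offered the existing web surveys and are analysed in their condition.
2. Report the number of crisis withdrawals by condition and period (waiting, AFFIRM, follow-up) from the existing crisis response forms. State whether any equivalent withdrawal applies during the wait.
3. Add a sensitivity analysis in which outcomes missing after crisis withdrawal are shifted to worse scores by a range of stated amounts.

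The surveys, links and forms already exist, so the practical cost is low. The real costs are ethics review of survey contact with vulnerable youth, some refusals (so the bias is reduced, not removed), and estimates that may be slightly less favourable to AFFIRM.
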